### Randomisation

Each participant’s screening and baseline data will be entered into a computerised central randomisation service by means of a secure 24/7 web interface. After the computer program has checked data for completeness and consistency, it will allocate the participant a unique study identification number and assign them to either the intervention or the control arm of the study. The system applies a minimisation program to achieve balance for three factors, namely, (i) time since stroke (as fatigue tends to improve over time; < 1 year versus ≥ 1 year) [3], (ii) sex (since fatigue tends to be more common in women) [30] and (iii) depression score at baseline (since those with more depressive symptoms may have more severe fatigue and so respond differently to the intervention) [11]. Minimisation on anxiety and fatigue will not be required because depression, anxiety and fatigue tend to be highly correlated [11].

The randomisation record will be stored within the trial database. Following randomisation to either the intervention or control arm, a letter will be sent to the participant’s GP to inform them of their patient’s enrolment in the trial with a copy of the signed participant consent form. The participant will be informed by telephone, email or post about the randomisation outcome. The intervention will commence within 2 weeks of randomisation, depending on the availability of therapist and participant.

### Intervention

This is a pragmatic trial. As stroke psychologists are scarce in the United Kingdom National Health Service (NHS) [31], it was decided that nurses or AHPs would be trained to deliver the intervention. The nurse/AHP therapists will receive standardised training from an experienced stroke clinical psychologist (DG) and fatigue expert and cognitive behavioural psychotherapist (TC) in how to deliver the intervention, and how to record the content of each session using a checklist. The 1-day training will comprise an overview of the literature on post-stroke fatigue as well as an introduction to the principles and practice of CBT, including role play and group discussion; reading materials for self-study will be also provided.

The delivery of the intervention will be by telephone. Trial materials (including written information about fatigue, a participant handbook, participant diary and follow-up questionnaires) have been made available on a trial website (www.ed.ac.uk/usher/edinburgh-clinical-trials/our-studies/all-current-studies/positif/the-positif-trial).

The intervention will be tailored towards the specific needs of participants, including their existing activity levels. For example, after the first session, the participant completes diaries to record activity and sleep. Then, based on those diaries, goals related to increasing activity and improving sleep are negotiated. The content of goals will be individualised and inevitably vary between participants. The participant handbook includes information sheets about how pain, medication and other medical conditions may be related to fatigue; participants will be sign-posted to the particular information relevant to them.

The intervention comprises six sessions, each separated by 2 weeks. In the intervals between sessions, it is suggested that participants work on their chosen goals. At the final session, participants reflect on any gains made, how they were achieved, discuss potential set-backs and make a plan to maintain and/or build on any behavioural changes they have made which may be influencing levels of fatigue. There is a review phone call two to four weeks after the sixth session, to check on progress and to offer ongoing encouragement. An outline of the content and main focus of each session is provided in Table 1.

**Table 1 Tab1:** Content of telephone-delivered cognitive behavioural therapy sessions

Session number	Treatment outline
1	**Engagement and preparation** ­ Discuss the patient’s experience of post-stroke fatigue ­ Explain symptoms and potential mechanisms of post-stroke fatigue ­ Emphasise that maintaining factors are potentially reversible ­ Explain how to use a diary to monitor daily activities, rest and sleep
2	**Balancing daily activities, rest and sleep** ­ Review diaries the patient has been keeping to determine current levels of activity, rest and sleep ­ Discuss strategies to improve sleep patterns ­ Set SMART goals to increase daily activities and improve sleep ­ Agree on an initial plan to balance activity levels, rest and sleep
3	**Increasing daily activities in graded increments** ­ Review the patient’s diary and discuss progress with the initial plan ­ Discuss new goals to be achieved in the coming weeks (including decreasing the amount of rest) ­ Agree on a weekly plan to work towards new goals
4	**Improving emotions and thoughts** ­ Discuss the ‘3-area model’ to explain the links between thoughts, emotions and behaviour ­ Discuss the unhelpful thoughts and emotions that might occur in response to fatigue ­ Introduce thought challenging sheets
5	**Dealing with difficulties in making progress** ­ Identify common ‘blocks’ and setbacks in making progress ­ Discuss any problems the patient has experienced and agree with the patient solutions (patient taking active role)
6	**Preparing for the future** ­ Check patient’s understanding of the intervention and discuss their progress ­ Encourage the patient to suggest new future targets and a plan for working towards them ­ Ask patient to fill out treatment evaluation forms
Booster (4 mo after starting intervention)	**Review of overall progress** ­ Evaluate the patient’s progress since session 6 ­ Help the patient solve any outstanding problems ­ Review the patient’s understanding of treatment rationale and skills ­ Discuss further targets and plans

All sessions will be audio recorded on encrypted voice dictation devices. Nurse/AHP therapists will receive fortnightly telephone supervision for the duration of the study (approximately 30 min per fortnight); the supervising psychologist (DG) will have the opportunity to listen to audio recordings before supervision sessions. Table 2 provides an overview of the rationale for the study, as well as study materials and procedures.

**Table 2 Tab2:** Overview of intervention rationale, materials and procedures

Brief name of intervention	**P**ost **S**troke **I**ntervention **T**rial **I**n **F**atigue (The POSITIF Trial)
**Why (rationale for treatment)**	Post-stroke fatigue is common, experienced by approximately half of all stroke survivors. It has a negative impact on a range of important life domains. A systematic review of the literature found that psychological factors, namely, depression, anxiety, low self-efficacy, passive coping, reduced physical activity, sleep problems and low levels of social support are implicated in the development or maintenance of fatigue following stroke. This evidence suggests that cognitive behavioural treatment methods, which target individuals’ thoughts, behaviours and feelings, and have been used to treat fatigue in other health conditions, could be effective in the treatment of post-stroke fatigue.
**What (materials)**	POSITIF is a manualised cognitive behaviourally informed treatment that targets the factors that have been associated with post-stroke fatigue in the literature. Individuals will receive a participant manual that includes written information about post-stroke fatigue, as well as activity and sleep diaries and worksheets for goal setting and thought challenging. Before POSITIF, the materials were provided to 12 stroke survivors in a small uncontrolled pilot study and edited to take account of participant and clinician feedback (see Table 1).
**What (procedures)**	Information will be provided to participants about post-stroke fatigue and individuals will be given an opportunity to discuss their ‘model’ of fatigue, i.e. why they believe they experience it. Any misconceptions about fatigue will be corrected. Activity diaries and sleep diaries will be completed by participants throughout the intervention and sent to the therapist (by post); these will form the basis for a tailored approach designed to promote a balance between daily activities, rest and sleep, the aims being to gradually increase levels of physical activity, and to avoid ‘boom and bust’ activity patterns. Therapists will identify participant beliefs about fatigue and help participants to challenge negative thinking, encouraging them overcome any fears about undertaking physical activity (see Table 1). The comparator group will receive written information about fatigue only, in the form of a leaflet (available at www.strokeassociation/dudfuhfud.com).
**Who (profession, expertise, specific training, etc)**	The intervention is to be delivered by nurses or Allied Health Professionals (AHPs). These therapists will be individuals with clinical experience of stroke, but no prior training in Cognitive Behavioural Therapy (CBT). They will be representative of the nurses who work with stroke survivors in community stroke settings. Therapists will receive a one-day training that comprises an overview of the literature on post-stroke fatigue, an introduction to the principles and practice of CBT, and information on how to deliver the intervention, including how to record the content of sessions. A stroke clinical psychologist and a cognitive behavioural psychotherapist will deliver the training. Brief role plays and group discussions will be included; reading materials, including journal articles will be provided to trial therapists for self-study. Nurse/AHP therapists will receive fortnightly telephone supervision (30-minutes duration) from the stroke clinical psychologist who delivers the training.
**How (modes of delivery)**	POSITIF sessions will be telephone-delivered. Phone calls will be made at times convenient to participants. Therapists will try to call participants at least two or three times before a session is classed as ‘missed’, as would happen in clinical practice. Participants will be required to have their written manuals in front of them during the calls so that therapists can direct them to particular worksheets and other materials.
**Where (infrastructure and relevant features)**	Participants will receive the telephone sessions in their own homes. They will receive the participant manuals by post.
**When and how much (number of sessions, duration, intensity, dose)**	The intervention comprises six sessions, one every two weeks. Sessions will be up to 60 minutes in duration. In the intervals between sessions, participants will work on their chosen goals. A review ‘booster’ telephone session will take place two to four weeks after the sixth session.
**Tailoring (personalisation)**	Goals will be individualised for each patient to take account of their baseline level of activity and sleep patterns, their physical health, levels of fatigue and their interests and aspirations.
**Modifications (from existing or initial protocol)**	Any modifications that are required in the course of the intervention will be recorded.
**How well (planned adherence)**	Adherence to the intervention will be determined as number of sessions each participant receives.

### Comparator

Careful consideration was given to the nature of the control intervention. As there is no effective intervention for post-stroke fatigue that is routinely available in clinical practice, it is not possible to compare the active intervention in POSITIF with another active intervention. A ‘placebo’ control intervention such as relaxation was considered, but would have required considerable additional resources to administer, and may have been less acceptable to participants [32]. A wait list design was also considered in which no intervention would be provided during the experimental treatment period, with active treatment offered after the final follow-up assessment, but this would also have needed additional resources. The participant handbook could have been provided to control participants at the end of the post-treatment assessment, but it was designed to be used with therapist input and could not be easily used by individuals without support and guidance. Finally, the control could have been ‘usual care’, but there were concerns that participants might decline the invitation to participate if there was a 50% probability of receiving nothing additional to routine care. Therefore, it was decided to provide control participants with information about fatigue. Although information about post-stroke fatigue is easily available (e.g. from charity websites), our clinical experience is that patients are not usually signposted to it. A Cochrane review of information provision after stroke reported that information alone has a very small, probably not clinically significant effect on depression, though there are no data on the effect of information provision on fatigue [33]. A copy of the information leaflet, given immediately following randomisation, can be found at https://www.stroke.org.uk/sites/default/files/fatigue_after_stroke.pdf.

Table 3 provides a summary of the timing of treatment telephone calls and feasibility study assessments.

**Table 3 Tab3:** Summary of study assessments and treatment telephone calls

	Study period										
	Enrolment	Allocation	Post-allocation							Close-out	
Timepoint (time in weeks)	−t1	0	1	3	5	7	9	11	14 (+/−1)^*^	16	26
Enrolment											
Consent and screening	X										
Randomisation	X										
Allocation		X									
Intervention											
Telephone call 1			X								
Telephone call 2				X							
Telephone call 3					X						
Telephone call 4						X					
Telephone call 5							X				
Telephone call 6								X			
Booster telephone call									X		
Assessments											
Baseline assessments											
Two fatigue screening questions PHQ-9 GAD-7 SF-SIS cognitive item SF-SIS language item Screening questions about serious illness		X									
4 months follow-up assessments											
FAS PHQ-9 GAD-7 CBRQ EQ-5D-5 L										X	
6 months follow-up assessments											
FAS PHQ-9 GAD-7 CBRQ SF-SIS EQ-5D-5 L Anxiolytics (Y/N) Hours working Health costs											X

*The booster treatment telephone call can take place at 13, 14 or 15 weeks post-randomisation

*CBRQ* Cognitive and Behavioural Responses Questionnaire, *EQ-5D-5 L* EuroQoL 5-dimension 5-level, *FAS* Fatigue Assessment Scale, *GAD-7* Generalized Anxiety Disorder Assessment 7-item, *PHQ-9* Patient Health Questionnaire 9-item, *SF-SIS* Short Form Stroke Impact Scale

### Feasibility outcomes

The following data will help to inform the design of a future main efficacy trial:

#### Recruitment

The feasibility of individuals referring themselves for fatigue screening via links to patient websites including CHSS and The Stroke Association (number and rate)The feasibility of identifying stroke survivors through local sites (number and rate) and the proportion who agree to fatigue screeningThe number of stroke survivors who complete the screening questions, according to the method by which they were identified (by local sites or self-identification)The proportion of individuals who undergo fatigue screening who are eligible to participateThe proportion of eligible patients who are randomisedThe recruitment rates by different methods and by different sitesThe feasibility of identifying and training nurses and AHPs to deliver the intervention

#### Adherence and retention

The adherence rate and reasons for non-adherence (number of sessions participants receive)The fidelity of the intervention (i.e. therapist adherence to the manual)

#### Data completion and data variability

The response and completion rates for postal and web-based questionnaires, and the proportion of participants requiring telephone calls to collect follow-up questionnairesVariability in our fatigue outcome measure

#### Resources

The resources required to deliver the intervention

A Data Monitoring Committee (DMC) will be established, and a DMC charter will be written. In this feasibility trial, the Trial Management Group (the investigators) will provide oversight of the trial and will function as a Trial Steering Committee (TSC).

### Progression criteria

We will proceed to an efficacy trial if the following criteria are achieved in the feasibility trial:
Recruit 75 participants in 1 year (from local sites and through self-referral, e.g. links with relevant websites)Follow-up (primary outcome in at least 90% of participants)Adherence to therapy: at least four of the six sessions attended

If these criteria are not met, the TMG will explore the reasons for this and may still proceed with an efficacy trial if the reasons are addressable, for example sick leave amongst therapists delivering the intervention.

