**Methods/design:**

POSITIF aims to recruit 75 stroke survivors between 3 months and 2 years post-stroke who would like treatment for their fatigue. Eligible consenting stroke survivors will be randomised to either a 7-session manualised telephone-delivered intervention based on CBT principles plus information about fatigue, or information only. The aims of the intervention are to (i) provide an explanation for post-stroke fatigue, in particular that it is potentially reversible (an educational approach), (ii) encourage participants to overcome the fear of taking physical activity and challenge negative thinking (a cognitive approach) and (iii) promote a balance between daily activities, rest and sleep and then gradually increase levels of physical activity (a behavioural approach). Fatigue, mood, quality of life, return to work and putative mediators will be assessed at baseline (just before randomisation), at the end of treatment and 6 months after randomisation. POSITIF will determine the feasibility of recruitment, adherence to the intervention and the resources required to deliver the intervention in a larger trial.

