**Discussion:**

The POSITIF feasibility trial will recruit until 31 January 2020. Data will inform the utility and design of a future adequately powered randomised controlled trial.

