## Methods

### Study registration

The study design was approved by the East of Scotland Research Ethics Committee (30 January 2018). The trial was registered with the U.S. National Institutes of Health on ClinicalTrials.gov (11 June 2018) with trial identification NCT03551327. Recruitment commenced in January 2019 and is currently ongoing.

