### Sample size

The recruitment period is 14 months, and we aim to recruit at least 75 participants in total from three hospital sites and online self-identification. This number is consistent with recommended sample sizes for pilot randomised controlled trials (RCTs) [24], 60–100 participants generally being required to estimate event rates in a single group. We will monitor recruitment rates closely so that any issues or barriers to recruitment can be identified and resolved.

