### Statistical analysis

We will report numbers and percentages for the tests of feasibility, without formal statistical testing.

For the proposed outcome measures for a future efficacy trial, in this feasibility study, we will present overall summaries across both treatment groups combined, such as mean and standard deviation, number and percentage and proportion of missing data. We will also test for differences between the randomised groups, but because this is a feasibility trial with a relatively small number of participants, we will refrain from drawing strong conclusions. A full statistical analysis plan will be written prior to database lock.

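### The recruitment criterion (75 in 1 year), the planned period (14 months) and the stated dates (12 to 13 months) do not agree

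*Protocol article*

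**What the plan says.** The protocol article describes the recruitment window in three ways.

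- **Progression criteria.** The first of three conditions is "Recruit 75 participants in 1 year", counting local sites and self-referral together. The list is introduced by "We will proceed to an efficacy trial if the following criteria are achieved in the feasibility trial". It is followed by a provision for a miss: "If these criteria are not met, the TMG will explore the reasons for this and may still proceed with an efficacy trial", on condition that the causes can be put right.
- **Sample size.** "The recruitment period is 14 months, and we aim to recruit at least 75 participants in total". The sources named there are hospitals (three of them) and people who put themselves forward online. The abstract gives the same figure without a duration: "POSITIF aims to recruit 75 stroke survivors between 3 months and 2 years post-stroke".
- **Dates.** Study registration says "Recruitment commenced in January 2019 and is currently ongoing". The abstract's discussion paragraph says "The POSITIF feasibility trial will recruit until 31 January 2020".

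The Trial design section puts recruitment rates first in the primary aim. It also says that results will be reported in line with the criteria set in advance. Under Statistical analysis, "We will report numbers and percentages for the tests of feasibility, without formal statistical testing".

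**The concern.** The same 75 participants, from the same sources, are attached to a 12-month window in one section and a 14-month window in another. The dates support a third length that cannot be 14 months. The article does not say that the criterion is read at month 12 of a longer period, that the extra two months are set-up time, or on what day the year begins.

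Feasibility results are not formally tested, so the verdict on this criterion is a plain comparison of a count with a threshold. The length and start of the window therefore decide the answer. A 75th participant in month 13 or 14 gives a trial that reached its target in the Sample size section and missed its threshold under Progression criteria. Recruitment is the first element of the primary aim and the first progression criterion, so a report could present that result as success or as a miss, depending on which section it cites.

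**Working it through.** **Inputs.** Target 75 (Sample size; abstract). Planned period 14 months (Sample size). Criterion 75 in 12 months (Progression criteria). Start January 2019, day not given (Study registration). End 31 January 2020 (abstract). No sample-size formula applies, because the target is not based on power.

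**Step 1: length of the calendar window.** Days are counted inclusively to 31 January 2020 and divided by 30.4375 days per month.

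| Assumed start | Days | Months |
|---|---|---|
| 1 January 2019 | 396 | 13.0 |
| 15 January 2019 | 382 | 12.6 |
| 31 January 2019 | 366 | 12.0 |

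No start day in January 2019 gives 14 months. A start at the very end of the month gives about 1 year, which agrees with the criterion but still not with the Sample size section.

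**Step 2: implied rates.** Rate = 75 / months.

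- Criterion: 75/12 = 6.25 per month.
- Sample size section: 75/14 = 5.36 per month.
- Dates: 75/13.0 = 5.77 per month for a start on 1 January, rising to about 6.25 for a start on 31 January.

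The criterion needs a rate 14/12 = 1.167 times the 14-month rate, that is 16.7% faster. Held for 14 months, it would give 6.25 × 14 = 87.5 participants.

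**Step 3: can the criterion's figure be reproduced from the 14-month plan?** Constant accrual is assumed here, since the article gives no accrual curve.

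- Expected by month 12 at the 14-month rate: 75 × 12/14 = 64.3.
- Shortfall: 75 − 64.3 = 10.7, and 10.7/75 = 14%.

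So 75 in 1 year does not follow from 75 in 14 months.

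**Step 4: illustration of chance variation.** If accrual is also Poisson, the probability of at least 75 by month 12 is:

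| Months taken to expect 75 | Expected by month 12 | P(at least 75) |
|---|---|---|
| 14 | 64.3 | 0.10 |
| 13 | 69.2 | 0.26 |
| 12 | 75.0 | 0.52 |

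**Step 5: what does not depend on the accrual pattern.** If the 75th participant is randomised after month 12 and by month 14, the Sample size target is met and the criterion is not, whatever the shape of the accrual curve.

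**The case against.** The best defence is that the two statements do different jobs. The Sample size section sets a minimum total and a duration; Progression criteria sets a threshold. A threshold stricter than the minimum target is not in itself contradictory, and a trial that reached 75 by month 12 and kept recruiting to month 14 would satisfy both. This stands in part. A reader might infer that a trial recruiting to plan is bound to fail its own criterion. The article does not support that, because the target is worded as a floor and no monthly rate is planned. The defence does not explain the dates, which cannot contain 14 months on any January start, and the article never says that a stricter threshold was intended.

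A reader might also infer that the window is open to choice once the count is known. That goes too far: only one section states a criterion, and it names 1 year. As written, 75 at month 14 is a miss. What is left open is when the year starts and why the planned period is longer.

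Nor is this a strict go/no-go rule. The Trial Management Group may proceed after a miss, and Trial design reports that the seamless move to an efficacy trial was dropped when further funding was not obtained. Both points lower the stakes. The criterion still frames how the results will be reported, and the discretion applies only once it is clear that a criterion was missed.

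Finally, the probabilities in step 4 are illustrative. The Participants section describes a retrospective pool used until it is exhausted alongside prospective and self-referral routes, so accrual need not be flat. Early use of that pool could narrow the month-12 shortfall; a slow start would widen it.

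**Conclusion.** The inconsistency is real and stated in the article's own figures: 12 months, 14 months, and dates spanning 12.0 to 13.0 months, with nothing to reconcile them. It affects the verdict on one of three progression criteria, the one tied to the leading feasibility aim. The part that needs no assumption is that a 75th participant arriving after month 12, within the planned period, meets the target and misses the criterion. The size, about 64 expected by month 12 or 14% short, assumes constant accrual at the 14-month rate.

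The documents do not support treating the calendar window as simply 13 months, which is the upper end of the range, nor treating the 10% and 26% probabilities as forecasts.

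Severity is moderate. The criterion is not binding, and randomisation and outcome data are unaffected. Recruitment rates by method and by site are already due to be reported.

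**What to change.** - Keep the 1-year criterion as set in advance. State the date on which the year starts and judge the criterion on the number randomised by month 12.
- Correct the 14-month period in the Sample size section, or explain it (for example, if it includes set-up time), so that it agrees with the start and end dates. Give the start day.
- Report the full-period count and monthly rate separately, and do not offer them as evidence that the criterion was met.
- Do not restate the criterion as 75 in 14 months. The article is dated 15 June 2020, after the stated close of recruitment on 31 January 2020, so this would lower the required rate from 6.25 to 5.36 per month after the event. If 14 months was always the intended window, document that openly, with its basis, before database lock; the article says the full statistical analysis plan will be written by then.

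The cost is a few sentences in the analysis plan and the trial report, and aligned dates. No new data are needed. The one consequence is that a count reaching 75 only after month 12 must be reported as a miss, with the reasons then considered under the existing provision.
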